The treatment of people with BPD is frequently characterized by conflicts with health professionals and such conflicts are particularly likely to arise in the management of self-harming behaviour [11]. Moreover, the cessation of self-harming behavious is often associated with an individual's ability to assert greater control over their life [12]. Given that the JCP is designed to facilitate a more collaborative relationship with staff, we hypothesise that JCPs may be an effective way of managing self-harm in people with BPD. In this article, we describe the proposed methods of an exploratory randomized controlled trial (RCT) that is designed to estimate the effectiveness and cost-effectiveness of JCPs on self-harming behaviour in people with BPD and to determine the most effective methods of data collection to inform future studies.

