#### Power calculation

Participants will be followed up for a minimum of six months with a predicted 36% and 12% of participants repeating self harm (including serious threats) in the TAU group and JCP intervention group respectively. On the basis of these predictions, an overall sample of 114 (randomised 1:1 to TAU: JCPs) would provide 80% power to detect an observed difference between TAU and JCPs based on a 2-sided test at the 5% significance level. This will be increased to 120 to allow a small loss in the administrative data on self-harm. This sample is also large enough to provide 80% power to detect a constant hazard ratio between the groups of 0.29 with proportions of events in the two groups as stated above, based on the log-rank statistic assuming no accrual rate, a fixed time of follow-up and an estimated 10% dropout.

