### Statistical analysis plan

An intention-to-treat analysis will be applied in the first instance (i.e. analysing all available data from randomised participants). The three data collection methods for the outcome of self-harm (i.e., participant interviews, diaries and electronic case records) are likely to differ on the amount of missing data. We will compare proportions of missing data using chi-square tests and agreement between data collection methods using Lin's Concordance Correlation Coefficient. Preliminary effectiveness estimates: Logistic regression will be used to compare proportions of patients that have self-harmed during the follow-up period in the two groups. Analysis of 'time to first self harm' outcome will also be conducted using survival analysis methods; log-rank test for bivariate comparisons and cox's proportional hazards to adjust for gender, stratification variables and time spent on treatment prior to randomisation. Other outcome assessments (continuous and binary) will be compared between the treatment groups at 6-month follow-up using t-tests, chi-square tests or non-parametric equivalents as appropriate, and regression modelling. The primary outcome analysis will be repeated on all three outcome collection methods to determine if conclusions remain the same. We expect little disparity in reporting of 'any self-harm episode' but potentially more in the time of first episode and number of episodes. If conclusions differ by the collection method used we will investigate reasons for the discrepancy. From this analysis we will be more certain of the appropriate collection methods for self-harm data and be better placed to decide on the appropriate outcome measure and estimate effectiveness in a future definitive trial.

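### Matching conclusions across the three self-harm sources is a weak guide to which source to use; compare the source-specific treatment effects, and report agreement by arm

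*Protocol article*

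**What the plan says.** The Background section of the protocol article gives as one purpose of the trial "to determine the most effective methods of data collection to inform future studies". The Statistical analysis plan section names the three sources as "participant interviews, diaries and electronic case records" and deals with them in two ways.

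- **Direct comparison of the recorded data:** "We will compare proportions of missing data using chi-square tests and agreement between data collection methods using Lin's Concordance Correlation Coefficient".
- **Comparison through the trial result:** "The primary outcome analysis will be repeated on all three outcome collection methods to determine if conclusions remain the same". The follow-up is "If conclusions differ by the collection method used we will investigate reasons for the discrepancy", and the section ends by stating "From this analysis we will be more certain of the appropriate collection methods for self-harm data".

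The analysis to be repeated is a logistic regression on any self-harm: "Logistic regression will be used to compare proportions of patients that have self-harmed during the follow-up period in the two groups". The section does not define a conclusion. The only testing level stated is in the Power calculation section: "based on a 2-sided test at the 5% significance level".

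**The concern.** Whether three tests on the same participants reach the same conclusion depends mainly on the size of the treatment effect and on how many events each source captures. It depends much less on whether the sources record the same behaviour. With no effect, all three tests are usually non-significant whatever the quality of the sources. With a real effect, a source that misses events can fall short of significance while estimating the same relative effect as the others.

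At stake is the choice of outcome source for the definitive trial. Matching conclusions could be taken as support for treating the sources as interchangeable. Differing conclusions could be taken as evidence that the sources disagree about the effect when they differ only in precision. Neither inference is sound. The primary comparison in this trial is not affected.

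**Working it through.** **Inputs from the protocol article.** 36% (TAU) v 12% (JCP), 80% power, two-sided 5%, 114 participants raised to 120, so 60 per arm; three sources.

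**Reproducing the stated sample size.** With mean proportion 0.24:

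n = [1.96·√(2·0.24·0.76) + 0.842·√(0.36·0.64 + 0.12·0.88)]² / 0.24² ≈ 48.5, so 49 per arm (98 in total).

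With continuity correction: n/4·[1 + √(1 + 4/(n·0.24))]² ≈ 56.5, so 57 per arm, 114 in total. The stated figure is reproduced.

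**Assumptions added here.** A conclusion is significance and direction from a two-sided 5% two-proportion test, standing in for a logistic regression with arm only. Each source misclassifies one true status independently of the others. Sensitivity and specificity are illustrative; the article gives none. There were 40,000 simulated trials per scenario (standard error at most √(0.25/40,000) = 0.0025).

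**Analytic floor.** For three unrelated sources and no effect, P(same) = 0.95³ + 2·0.025³ ≈ 0.857.

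**Simulated probability that all three conclusions match:**

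| Sources | No effect, 36% v 36% | 36% v 12% |
|---|---|---|
| Near-perfect (sens. 97%, spec. 99%; kappa about 0.93) | 95% | 89% |
| Good (sens. 95/90/90%, spec. 98%; kappa about 0.8) | 92% | 79-80% |
| Sens. 95/80/50%, spec. 100% (kappa 0.51-0.81) | 89% | 58% |
| Sens. 90/60/30%, spec. 100% (kappa 0.30-0.62) | 87-88% | 36-37% |
| Unrelated to each other within arm | 86% | 71% |

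Kappas are those under no effect. In that column, the whole range from near-perfect sources to noise spans 95 - 86 = 9 percentage points.

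**Same relative effect, different conclusions.** At sensitivities of 95/80/50% with specificity 100%, the expected rates are 34.2% v 11.4%, 28.8% v 9.6% and 18% v 6%. The risk ratio is 0.333 in each. Powers are about 87%, 78% and 54%, and the conclusions differ 100 - 58 = 42% of the time. That comes from lost power alone.

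**What pooled agreement can and cannot show.** For a binary outcome with source proportions p and q, Lin's coefficient is 2(p11 - pq)/[p(1-p) + q(1-q) + (p-q)²]. The denominator reduces to p(1-q) + q(1-p), so the coefficient equals Cohen's kappa. It would therefore reveal the poor scenarios above. Now take no true effect, interview and diary sensitivities of 95% and 90%, and a records sensitivity of 60% in TAU and 85% in JCP:

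- The expected records rates are 0.36·0.60 = 21.6% v 0.36·0.85 = 30.6%, a spurious difference.
- The pooled kappas are 0.89, 0.75 and 0.72, the same as with a uniform records sensitivity of (60 + 85)/2 = 72.5%.
- Records are falsely significant 20-21% of the time, yet the three conclusions still match 77% of the time.

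The article gives a possible route to such a difference. Under Administration of the experimental intervention, the plan is attached to the participant's electronic record; under Self-harm follow-up data, that record is one of the three sources.

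**The case against.** The strongest reply is that the article fixes no selection rule. It describes a sensitivity analysis in an exploratory trial, sets no threshold, does not equate a conclusion with a p-value, and attaches only an investigation to a difference. The closing statement about greater certainty can be read as covering the whole paragraph, including agreement and missingness. This stands: the percentages above hold only on the 5% significance reading.

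A reader might infer that a null trial would leave badly disagreeing sources undetected. The document does not support that. Lin's coefficient, which is kappa for this outcome, and the missing-data tests are planned regardless of the trial result and would expose gross disagreement. Nor does the text say that a discrepancy will be looked into only when conclusions differ.

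Two further points have force. Under the planned effect the check does separate related sources (89%, 80%, 58%, 37%); the reversal occurs only against wholly unrelated sources (71%), which is unlikely for three records of the same behaviour. Also, a source that loses much power is a fair candidate for rejection. But low capture is better read from capture itself than from which side of 0.05 a p-value falls.

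Finally, the form of a between-source model is ordinary SAP content, and its absence from an article is no fault. The point concerns the criterion that the article does state.

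**Conclusion.** The point holds in a limited form. On the assumption that a conclusion is significance at 5%, matching conclusions are a weak criterion for comparing the sources: with no effect, about 86-89% for unrelated or poorly agreeing sources against 92-95% for good or near-perfect ones. Under 36% v 12%, sources with an identical risk ratio differ about 42% of the time in the 95/80/50% example. Source accuracies and independent misclassification are assumptions.

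It would be wrong to say that matches reach 95% for sources that disagree badly; that figure belongs to near-perfect sources. It would also be wrong to say that the plan has no direct check of agreement. The gap that remains is that the planned checks, as described, are not by arm and do not compare treatment effects, so capture that differs between arms can go unseen. This is a worthwhile, inexpensive improvement, not a flaw in the primary analysis.

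**What to change.** Keep the by-source analyses, Lin's coefficient and the missing-data comparison. Then:

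1. Replace the aim of seeing whether conclusions match with a comparison of the source-specific treatment effects and their 95% CIs.
2. Estimate the between-source contrast within participant: stack the three yes/no outcomes in one marginal model clustered on participant, with arm, source and arm-by-source terms, and report the ratios of effects with 95% CIs.
3. Prefer the risk-ratio scale. Odds ratios differ between sources that share a risk ratio: (0.12/0.88)/(0.36/0.64) = 0.24 at 36% v 12%, but (0.06/0.94)/(0.18/0.82) = 0.29 at 18% v 6%.
4. Report agreement and capture (positive in one source given positive in another) by arm.
5. Base the choice of source on these together with missingness. State that matching or differing significance is not itself evidence about the sources, and investigate discrepancies whether or not the p-values fall on the same side of 0.05.

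The cost is some wording and one extra model on data already being collected. The drawback is that the between-source ratios will have wide intervals at N = 120, so the trial may have to report that interchangeability was not shown.

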### Economic evaluation

The economic evaluation will take a broad perspective, including the cost of all hospital and community health and social care services and contacts with the criminal justice system. Resource use information will be collected using a modified version of the Adult Service Use Schedule (AD-SUS) [23]. These data will also allow us to record what TAU was actually delivered during the trial. Resource use data will be combined with appropriate national unit costs to calculate the total cost of the intervention and control groups. The cost of the JCP will be directly calculated from salaries using a micro-costing approach [26]. Differences in mean total costs between groups will be compared using the standard t-test with ordinary least squares regression used for adjusted analyses and the validity of results confirmed using bootstrapping [27]. The cost-effectiveness of the intervention will be assessed through the calculation of incremental cost effectiveness ratios, using the primary outcome measure and cost-utility will be assessed through the calculation of QALYs based on the EQ-5D. Uncertainty around the cost and effectiveness estimates will be represented using cost-effectiveness acceptability curves [28].

### Process evaluation

A qualitative study will be carried out to explore the processes through which JCPs work in practice. Negotiating JCP content may clarify treatment issues and build consensus between service users and staff. However effects on trust, service user engagement in the process of care including shared decision making, changes to service user self esteem and empowerment, clearer channels of communication between all parties, changes to staff risk perception and/or changes within the culture of the mental health service may also be important. Focus groups will be used to examine people's experience of the JCP and separate service user and health professional focus groups will be convened. We anticipate involving approximately 5-10 service users and 5-10 staff in each of the two groups.

### Ethics

The study protocol was approved by South London REC Office (REC number: 09/H0803/113).

## Discussion

Joint Crisis Plans have been shown to to be an effective way of reducing compulsory treatment in people with psychosis, but to date, no study has examined their effectiveness in people with BPD. Despite the fact that BPD is a prevalent condition associated with increased mortality and substantial economic costs, treatment research in this area is still in its infancy. Complex psychological interventions have been shown to be useful [29], although such treatments are expensive and time-consuming to deliver and this has limited their availability. Less complex interventions are required for the large proportion of BPD people who are not referred to specialist services and JCPs may be an effective and cost-effective intervention [30]. We undertook detailed developmental work with service users, clinicians and academics in order to modify JCPs for people with BPD and to test the feasibility of developing such JCPs in a busy clinical environment. The plans proved to be both feasible and potentially useful and we now plan to test the effectiveness of JCPs in the exploratory trial.

The exploratory trial will gather critical information about key trial parameters necessary to inform the design of a definitive trial, including information on candidate outcome variables, consent and attrition rates and the acceptability of randomising people with BPD. Regarding our choice of primary outcome, currently, there is no gold standard for reliably measuring episodes of self-harm [31]. Accordingly, and to enhance the validity of our data, we will be making use of both contemporaneous and retrospective methods to measure self-harm including self-report, completion of diaries and electronic patient records. It is equally possible that whilst the JCP may not influence self-harming behaviour per se, the production of a JCP might lead to improvements in engagement with services and/or greater satisfaction in the management of future self-harm events. For these reasons, we will also be measuring these outcome domains as secondary outcome variables.

The JOSHUA study has limitations which warrant mentioning. Firstly, it is not a double-blind study design and, as such, the participants and certain members of the research team will be aware of which arm of the trial each participant has been allocated to. However, collection and analysis of follow-up data will be blind to treatment status. In addition there will be specific instructions to participants and clinical teams not to disclose treatment details details at any stage throughout the study. Every effort will be made to maximise the single blindness of research workers, whose 'best guesses' of service user status will be assessed after the final assessment/at the end of the study to test whether their blindness has been maintained. Secondly, there may be selective dropout in one arm of the study; as such, we will examine whether this occurred in the data analysis. Finally it is not designed as a definitive trial but one which will give broad indications of effectiveness and aid the design of a future trial.

## Abbreviations

AD-SUS: Adult Service Use Scale; AUDIT: Alcohol Use Disorders Identification Test; BPD: Borderline Personality Disorder; CMHT: Community Mental Health Team; EQ-5D: EuroQol 5 Dimensions (quality of life measure); HADS: Hospital Anxiety and Depression Scale; JCP: Joint Crisis Plan; SCIDD-II: Structured Clinical Interview for DSM-IV (v. 2.0); WAI: Working Alliance Inventory; WSAS: Work and Social Adjustment Scale.
